**C. Preliminary Studies/Progress Report**

Currently, there is not pilot results from human participants.

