**D. Research Design and Methods**

**Clinical trial design:** We will test the primary hypothesis that TRE improves NVC responses and endothelial function in older adults. This hypothesis will be tested by assessing the effects of TRE (10 hours eating window) in community dwelling older adults (55-80 years of age) in a 6-month study. At screening (Visit 0), participants will be evaluated for eligibility criteria, after obtaining informed consent. Individuals

will be asked report medications or supplements intake. Screening assessments and baseline physiological assessments may be conducted at that same visit (baseline, Visit 1) if all eligibility criteria are met, or within 4 weeks of Visit 0 (screening window) at the discretion of the investigator, when eligibility will be again confirmed. After baseline, the first fMRI and dual X-ray absorptiometry (DXA) scan visits will be performed, if the participant opts in to these measurements.

Upon completion of baseline physiologic measurements, all participants will be instructed to maintain TRE for the ensuing 6 months. Participants will be instructed on how to adhere to the TRE protocol. Participants will be evaluated at the Translational Geroscience Laboratory at the end of the protocol, at month 6 (-14/+14 days), when all physiologic assessment will be repeated (Visit 2). If participants terminate the protocol early for any reason, they will be invited to an early termination visit (ETV), which will include repeat physiologic and other evaluations same as in Visit 2. After visit 2, the second fMRI and DXA scan visits will be performed. As stated in the protocol and consent form, MRI and DXA scan visits are optional.

**Power analysis:** Based on our preliminary data analysis, a total of 27 eligible participants will provide 80% power for detecting a decrease of 7.4 in fNIRS against the null hypothesis of no change. A standard deviation of 13.1 was used in the calculation. After adjusting for a 20% dropout, the total of 32 participants will be enrolled. We will use intent-to-treat approach, wherein every participant will be included in the analysis regardless of whether participant is on or off the TRE for the final visit. To control for potential confounding, we will account for BMI, depression, the use of opiates, and other non-exclusive chronic conditions.

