**M. Statistical Methods**

There are currently no published data available on the effect of TRE on NVC responses in healthy young and older adults. Data obtained from this project will be used as preliminary data for an NIH application.

*Functional near infrared spectroscopy and dynamic retinal vessel analysis:* fNIRS data will be analyzed using a pipeline based on General Linear Model (GLM) approach created using the Brain AnalyzIR toolbox. After conversion of optical densities to change of hemoglobin concentration using the Beer-Lambert law, pre-whitening of data with an autoregressive model-based algorithm, and a discrete cosine transformation using high-pass filter, design matrices will be convolved with a canonical hemodynamic response function to predict brain activation. Parameter estimates (beta-weights), scaling the predictors, will be then used for group level statistics. Group level statistics will be performed using a repeated measures mixed effects model. The model will be defined in a Wilkinson-Rogers formula of 'beta ~ -1 + Group +(1|Subject)'. Output of the mixed effects model statistics will be used for a t test. Increased activation/NVC responses will be considered significant where false discovery rate corrected  $q < 0.05$ . When appropriate, beta values from corresponding channels to the cognitive task will be summarized using mean ( $\pm$ SEM) by group and study visit. We will use repeated measures mixed effects models (with a random subject effect) to assess the main effect of group (TRE vs. control) on NVC responses.

For DVA analysis, each participant will be evaluated for mean maximal arteriolar dilation and mean maximal venular dilation in response to flicker light stimulation. The statistical mean of 3 consecutive examinations will be calculated for each subject and each evaluated parameter as previously described. Data will be summarized using mean ( $\pm$ SEM) by group and study visit. We will use GLM with control and TRE treatment as between-group factor, and Visit 1 and Visit 2 as repeated measures (within group) factor. For post-hoc analysis, we will perform the Bonferroni test. The level of significance will be regarded as  $p < 0.05$ .

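### The 80% power is for a decrease in one unnamed fNIRS value tested once, which matches neither the increase-at-FDR rule nor the TRE-versus-control model in Section M

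*Protocol*

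**What the plan says.** The Power analysis paragraph of Section D states that "a total of 27 eligible participants will provide 80% power", the effect being given as "80% power for detecting a decrease of 7.4 in fNIRS against the null hypothesis of no change". It adds: "A standard deviation of 13.1 was used in the calculation". The inputs are introduced with "Based on our preliminary data analysis". No unit, haemoglobin species, task, n-back load, channel or region is attached to the 7.4, and alpha and sidedness are not given.

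The same section states the primary hypothesis as an improvement in NVC responses and puts all participants on TRE. Section B expects restored NVC and higher cerebral blood flow. Study 1 records fNIRS during an n-back task and also during a motor or other task, and names none as primary.

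Section M describes two fNIRS analyses in one paragraph:

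- A channel-level GLM pipeline leads to a mixed model and a t-test. Its rule is "Increased activation/NVC responses will be considered significant where false discovery rate corrected" q is below 0.05.
- Betas from task-related channels may be averaged where appropriate. A repeated-measures mixed model then assesses the main effect of group, TRE against control, with no direction and no FDR correction.

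Section C says: "Currently, there is not pilot results from human participants".

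**The concern.** A power statement is useful only if it refers to the test that will decide the result. Three things do not line up.

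- **Direction.** The trial is powered for a fall, the hypothesis is an improvement, and the only directional rule is for a rise. No fNIRS measure is named for which a fall would be favourable.
- **Test.** The power calculation concerns one number, whereas an FDR-corrected q implies a family of tests. The other model in Section M compares TRE with a control group that the all-TRE design in Section D does not contain.
- **Source.** The effect and SD are credited to preliminary data, while Section C reports no human pilot results.

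At stake is whether a reader can tell in advance which fNIRS result would support the hypothesis, and whether 80% applies to it.

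**Working it through.** **Inputs.** From Section D: change 7.4, SD 13.1, n = 27, power 80%. Not stated, so assumed: 13.1 is the SD of the within-person change, and alpha is 0.05 two-sided. These assumptions are adopted because they return the stated 27.

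**Reproducing the 27.**

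- Standardised effect: d = 7.4/13.1 = 0.565.
- Paired t-test, n = 27: noncentrality = 0.565 × √27 = 2.935; critical t on 26 df = 2.056; power = 80.7%.
- At n = 26 the power is 79.1%, so 27 is the smallest n that reaches 80%.
- Other forms tried do not give 27. Two-sided normal approximation: 24.6, so 25. One-sided t: 21. One-sided normal: 20. Two-group comparison: 2 × 24.6 = 49.2, so 50 per group.

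The stated figure is therefore one unadjusted two-sided test of one within-person change. Being two-sided, it needs the same 27 for a rise of 7.4 as for a fall.

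**Against the FDR rule.** The number of channels m is not stated; 4, 10 and 20 are assumed. It is also assumed that 7.4/13.1 applies to each responding channel. If one channel responds, the Benjamini-Hochberg threshold is approximately 0.05/m, and power follows from the same noncentral t. For half or all channels responding, the procedure was simulated with n = 27 and d = 0.565. Entries are power per responding channel, and the pairs are independent channels / between-channel correlation 0.5.

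| m | one responds (0.05/m) | half respond | all respond |
|---|---|---|---|
| 4 | 60% | 69% / 68% | 78% / 76% |
| 10 | 46% | 66% / 64% | 77% / 75% |
| 20 | 37% | 65% / 63% | 77% / 74% |

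If success instead means flagging at least one truly responding channel, the figures are higher. With half responding, the chance is at least 86% for independent channels and about 79% or more at correlation 0.5.

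If one averaged beta is the sole primary value, m = 1 and 80.7% stands.

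**Against the TRE-versus-control model.** The same inputs split into two equal groups (27/2 = 13.5 each) give about 29% power for a two-sample t-test. This is only an illustration that the 80% does not carry over, because Section D has no control arm.

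**Source of the inputs.** Section D credits preliminary data. Section C reports no human pilot results, Section M says nothing is published on TRE and NVC, and Study 4 in Section D describes its preliminary data as preclinical. No passage identifies where 7.4 and 13.1 come from.

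**The case against.** **Increases are not said to be the only result that counts.** A reader might infer that a true fall of 7.4 would have essentially no chance of success; the probability of a significant rise would indeed be below one in a million. The documents do not support that inference. The FDR sentence closes the description of an activation-mapping pipeline whose model has no intercept and no visit term, so it may simply ask whether activation differs from zero. The group comparison that follows has no direction and no FDR. This part of the objection stands. It does not rescue the 80%, because that comparison is TRE against control and is not the powered test either.

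**The sample size is not shown to be wrong.** This stands: 27 is correct for the test it describes, and the direction conflict leaves it unchanged. A fall could be favourable for some haemoglobin measure, but the protocol does not say that this is what it means.

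**The 60% to 37% range is a worst case.** This stands. It requires exactly one responding channel and an assumed channel count, so it should not be read as the trial's power.

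**The source statements may be compatible.** A reader might take Sections C and D as a proven contradiction. Earlier human fNIRS data without TRE could reconcile them, so the inconsistency is unexplained rather than proven. Nor does anything show that 13.1 is too small.

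**Haemoglobin species, n-back load and channel set may be left to an SAP.** This is fair for those details. It does not cover a protocol whose power paragraph and fNIRS rules point to different tests, because an SAP could not follow both as written.

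**Conclusion.** The concern holds as a mismatch between the power statement and the fNIRS analysis rules. The 80% belongs to a single unadjusted two-sided paired test of an unnamed value, with a stated direction that does not fit the improvement hypothesis unless a particular measure is meant. It does not describe the FDR rule or the TRE-versus-control model.

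The size of the loss cannot be fixed from the document. Under the assumed 4 to 20 channels, per-channel power runs from 37% (one of 20 responding) to 78% (all of four responding), and there is no loss if one averaged value is made primary. The origin of 7.4 and 13.1 is unclear. The step from 27 to 32 enrolled is a separate matter and is not used here.

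**What to change.** In Sections D and M:

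1. Name one primary fNIRS value. One option is the mean beta over a prespecified set of task channels, in one task and for one haemoglobin species, as Visit 2 minus Visit 1. That matches the all-TRE design in Section D. Section M currently averages channels only where appropriate, so the averaging would have to be made mandatory.
2. State the direction of benefit for that value. Either correct the word decrease or name the measure for which a decrease is improvement.
3. Test it once, two-sided at 0.05, and make the channel-wise FDR maps secondary. The calculation for 27 then describes the deciding test, provided that 7.4 and 13.1 refer to that value.
4. Reconcile the TRE-versus-control wording in Section M with this within-person test. If a control group is intended, the power calculation must be redone for that comparison.
5. Give the source of 7.4 and 13.1 and explain how it fits with Section C, or label both as assumptions.

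The cost is wording, with no new data. The drawback is that the channel-level maps lose confirmatory status.

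### Enrolling 32 does not follow from 27 evaluable participants and 20% dropout: it covers about 15% loss, and at 20% loss power is about 77–79%

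*Protocol*

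**What the plan says.** The power analysis in Section D (Research Design and Methods) gives the sample size in three steps.

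- Base size: "a total of 27 eligible participants will provide 80% power".
- Target and spread: the aim is "detecting a decrease of 7.4 in fNIRS against the null hypothesis of no change", and "A standard deviation of 13.1 was used in the calculation".
- Inflation: "After adjusting for a 20% dropout, the total of 32 participants will be enrolled".

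The paragraph gives no significance level, no sidedness and no inflation formula, and does not say whether 13.1 is the SD of the change or of a single measurement. The 0.05 level appears only in Section M, for individual analyses such as the retinal vessel analysis.

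Two other statements in Section D bear on the point. The design described there is single-group and pre-post: "all participants will be instructed to maintain TRE for the ensuing 6 months". For participants who stop early, "they will be invited to an early termination visit (ETV), which will include repeat physiologic and other evaluations same as in Visit 2". The section also plans an intent-to-treat analysis that keeps participants whether or not they are still on the eating regimen at the final visit.

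**The concern.** The base size, the dropout rate and the enrolment figure are printed together, and the third should follow from the first two. It does not. Dropout is a fraction of those enrolled, so the base size has to be divided by the fraction retained. Adding 20% of the base size gives a smaller number, and here that smaller number was also rounded down.

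At stake is whether the enrolment target delivers the stated power under the plan's own assumptions. Section M says the data will serve as preliminary data for a grant application, so the calculation is likely to be read again by people who will check it.

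**Working it through.** **Inputs from Section D.** Evaluable size 27; power 80%; change 7.4; SD 13.1; dropout 20%; enrolled 32.

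**Assumptions, not stated in the power paragraph.** One-sample (paired) t-test of the change, two-sided 0.05, with 13.1 as the SD of the change.

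**Step 1: reproduce 27.** The standardised change is 7.4/13.1 = 0.565. Power comes from the noncentral t distribution with n − 1 degrees of freedom and noncentrality 0.565 × √n.

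| Evaluable n | Power, two-sided 0.05 | Change detectable with 80% power |
|---|---|---|
| 25 | 77.3% | 7.65 |
| 26 | 79.1% | 7.49 |
| 27 | 80.7% | 7.34 |

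The smallest n that reaches 80% is 27, which is the protocol's figure. Other settings do not give 27: the two-sided normal approximation gives (13.1 × (1.960 + 0.842)/7.4)² = 24.6, so 25; a one-sided t-test at 0.05 gives 21; a two-sample comparison gives 50 per arm. The assumed setting is therefore the most likely one, but it remains an inference.

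**Step 2: inflate for dropout.**

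- Enrolment needed: 27/(1 − 0.20) = 33.75, so 34. Check: 34 × 0.80 = 27.2.
- Likely origin of 32: 27 × 1.2 = 32.4, rounded down. Rounding up on that formula would have given 33.

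**Step 3: what 32 provides.**

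- Expected evaluable at 20% loss: 32 × 0.80 = 25.6, so 25 or 26.
- Loss that still leaves 27: (32 − 27)/32 = 15.6%.

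Steps 2 and 3 use only the printed numbers and need none of the assumptions above.

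**Step 4: effect on power.** From the table, power at 20% loss is 77.3% to 79.1%. If each participant independently completes with probability 0.8, the number of completers is Binomial(n, 0.8):

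| Enrolled | Probability of at least 27 completers | Average power |
|---|---|---|
| 32 | 36% | 78.1% |
| 34 | 63% | 80.7% |

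The shortfall against 80% is 80 − 79.1 = 0.9 points with 26, 80 − 78.1 = 1.9 points on average, and 80 − 77.3 = 2.7 points with 25.

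**The case against.** **The gap is too small to matter.** It is two enrolled participants and about 1 to 3 points of power. At n = 27, the same loss of power would come from an SD of 13.4 (equivalent to 26 evaluable) or 13.7 (equivalent to 25) instead of 13.1. Section C says there are no pilot results from human participants, so the SD is not known that closely. This stands as an argument about size. It does not make 32 follow from 27 and 20%.

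**Stopping early is not the same as having no outcome.** Participants who stop are invited to a visit with the Visit 2 assessments, and those off the regimen stay in the analysis. Actual loss of data could therefore be below 20%, which makes 25–26 a conditional figure. But attendance is by invitation, and the intent-to-treat statement supplies no outcome for someone who is never reassessed. If 20% counts people who stop but are still measured, it is not the rate to inflate for, and the text should give the lower rate.

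**The power figures rest on unstated settings.** This is correct. With a one-sided 0.05 test, power would be 86.4% at 25 and 87.6% at 26; with the normal approximation, 80.6% and 82.1%. Neither setting yields the stated 27, so neither is likely to be the one used, but any restated power should carry its assumptions.

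**The recalculated power is not that of the planned analysis.** Section D adds covariates, and Section M describes models comparing the eating regimen with a control. The figures here check the protocol's own one-sample calculation and nothing more.

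A reader might go further and infer that the trial is materially underpowered, or that recruitment has to rise. The documents do not support either: the shortfall is small, it arises only if the full 20% is lost as missing outcome data, and a corrected sentence resolves the mismatch.

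**Conclusion.** The enrolment figure is wrong as written. With 27 evaluable and 20% dropout the number is 34; 32 covers a loss of 15.6%. This part is plain arithmetic on the protocol's figures.

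The consequence is small and conditional. If 20% of outcome data are lost, 25–26 participants remain and power for a change of 7.4 is about 77–79%, 78% on average, instead of 80%. That rests on a one-sample (paired) t-test, two-sided 0.05 and an SD of the change of 13.1. To say flatly that the stated 80% power is not delivered would overstate this: 32 does retain 27, and with them the stated power, as long as no more than 5 of the 32 are lost.

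**What to change.** Restate the inflation sentence in the power analysis, for example:

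> An enrolment of 32 retains 27 evaluable participants with up to about 15% loss of outcome data. With 20% loss, 25–26 remain and power is about 77–79% for a change of 7.4 (two-sided 0.05, SD of change 13.1).

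The sponsor should first confirm that the significance level, sidedness and meaning of 13.1 are those actually used. The cost is one sentence and a slightly less favourable power statement, with no additional participants. If the sponsor prefers to keep the 20% wording and the 80% power, the matching enrolment is 34, two more than now stated.

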For EEG analysis, the power spectral density of EEG records (obtain during n-back stimulation) will be estimated using the Welch's method and then averaged across 14 channels of the Emotive EPOC research instrument. Spectra will be plotted in a semilogarithmic graph as a function of EEG frequency. For channel-wise comparison, Lilliefors tests will be applied to verify normality of the data. For normally distributed data,  $F$  test will be then used to confirm equality of variances between groups, and the two-sample  $t$  test or the Welch-corrected  $t$  test will be applied for equal or unequal variances, respectively. For not normally distributed data, a Mann-Whitney  $U$  test will be used for group comparison. The false discovery rate (FDR) method of Benjamini and Hochberga will be applied to control for multiple comparisons.

*Peripheral endothelial function:* For analysis of micro- and macrovascular endothelial function, all data will be corrected for mean arterial pressure. Laser speckle data will be normalized to an average of 3 measurements of skin temperature taken before the start of the assessment. For microvascular endothelial function, we will evaluate the maximal perfusion over the baseline perfusion (x-fold change) and the acute

reperfusion index (over the first 4 seconds of cuff release) in the nailbeds and the hand as previously described. For macrovascular endothelial function, change in the brachial artery diameter over the baseline will be calculated (% change), as previously described. When appropriate, data will be summarized using mean ( $\pm$ SEM) by group and study visit. We will use GLM for between-group factor and repeated measures (within group) factor. For post-hoc analysis, we will perform the Bonferroni test. The level of significance will be regarded as  $p < 0.05$ .

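### The repeated-measures GLM for DVA, endothelial function and cognition, fitted on complete pairs as is conventional, cannot include participants with no second measurement and so fits poorly with the intent-to-treat statement

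*Protocol*

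**What the plan says.** Protocol Section D (Power analysis) adopts intent-to-treat, so that "every participant will be included in the analysis regardless of whether participant is on or off the TRE for the final visit". The same paragraph plans for attrition: "After adjusting for a 20% dropout, the total of 32 participants will be enrolled". Section D (Clinical trial design) invites anyone who stops early to an ETV, "which will include repeat physiologic and other evaluations same as in Visit 2".

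Section M (Statistical Methods) names two kinds of model:

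- **fNIRS:** "We will use repeated measures mixed effects models (with a random subject effect) to assess the main effect of group (TRE vs. control) on NVC".
- **DVA:** "We will use GLM with control and TRE treatment as between-group factor, and Visit 1 and Visit 2 as repeated measures (within group) factor".
- **Peripheral endothelial function (laser speckle, FMD) and cognitive performance:** the same sentence in both paragraphs, "We will use GLM for between-group factor and repeated measures (within group) factor".

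The protocol does not say how the GLM is to be fitted, or whether an ETV value takes the place of Visit 2.

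**The concern.** A conventional repeated-measures GLM holds one row per participant, with one column per visit, and a participant with an empty column is not analysed. With two visits it works on complete pairs. The protocol expects some participants to leave, so it has chosen, for three groups of outcomes, a model that may be unable to include everyone its analysis-set statement refers to. In the same section it gives fNIRS a model that can.

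These outcomes are not peripheral. The primary hypothesis in Section D covers NVC responses and endothelial function. Endothelial function is analysed by GLM, and so is DVA, which Study 1 lists among the NVC measures. At stake are some precision and, if those who leave differ at baseline from those who stay, the estimated pre-post change itself.

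**Working it through.** **1. The plan's own figure.** Inputs from Section D: change 7.4, SD 13.1, power 80%. Assuming a paired t test at two-sided 0.05 (sidedness is not stated), the noncentral t distribution gives n = 27 with power 0.807. The stated 27 reproduces, so the calculation is one of within-person change.

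**2. How many the GLM could leave out.** With 32 enrolled and 20% dropout, complete pairs number 32 × 0.80 = 25.6, that is 25 or 26, and 32 × 0.20 = 6.4, that is 6 or 7, have no Visit 2. ETV attendance is not given, so it is shown as a range, assuming that attended ETV values are used as the second measurement:

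| Dropouts attending the ETV | Left out of the GLM |
|---|---|
| 0% | 6.4 (6–7) |
| 50% | 3.2 (about 3) |
| 100% | 0 |

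A likelihood-based mixed model keeps all 32 who have a baseline value in every row.

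**3. Precision when dropout is unrelated to baseline.** No SD is given for DVA, laser speckle, FMD or cognition, so the fNIRS scale serves as illustration only. Assume equal variances at the two visits and correlation ρ = 0.5. Then Var(change) = 2σ²(1 − ρ) = σ², so σ = 13.1. With m = 25.6 pairs among n = 32 and no ETV data:

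- Complete pairs: SE = 13.1/√25.6 = 2.59.
- Likelihood-based: SE = σ√[(1 − ρ²)/m + (1 − ρ)²/n] = 13.1 × √(0.75/25.6 + 0.25/32) = 2.52.

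Simulation of 20,000 trials under these assumptions gave 2.58 and 2.53, in agreement. The gain is 2 to 3%, and both estimates are unbiased.

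**4. Bias when dropout depends on baseline.** If completers' mean baseline exceeds that of all participants by δ, their expected change is Δ − (1 − ρ)δ, where Δ is the true change. Assume that the odds of dropout double or triple per SD lower baseline, with overall dropout held at 20% and no ETV data. Then δ is about 0.128 or 0.185 SD, that is 1.68 or 2.42, and the shift is −0.5δ = −0.84 or −1.21:

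| Odds ratio per SD | True change +7.4 | True change −7.4 |
|---|---|---|
| 2 | 7.4 − 0.84 = 6.56 | −7.4 − 0.84 = −8.24 |
| 3 | 7.4 − 1.21 = 6.19 | −7.4 − 1.21 = −8.61 |

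The shift is the same, but it shrinks a rise and exaggerates a fall. In simulation the likelihood-based estimate stayed at about 7.4 under the same dropout. If half the dropouts attended the ETV and their values were used, the complete-pairs change for +7.4 was about 7.0 or 6.9, a bias of 5% or 7%.

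**The case against.** Four points can be made for the plan.

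- **The intent-to-treat sentence is worded around adherence.** It speaks of being on or off TRE at the final visit, and a participant who has stopped TRE but attends Visit 2 stays in the GLM. A reader might infer a flat contradiction, but the wording does not go that far. What stands is a poor fit between the opening promise to include every participant and a model that may not do so.
- **The ETV exists to obtain a second measurement from those who leave.** A reader might infer that everyone without Visit 2 is dropped and that these analyses are completers-only. That holds only if nobody attends the ETV or its data are discarded, and the protocol says neither. The ETV shrinks the problem but need not remove it, since attendance is by invitation.
- **Deletion is inferred, not stated.** No fitting method is named, and rules for missing data are commonly left to the SAP, which is not shown. Their absence is therefore not the point. The point is the model that the protocol itself names.
- **The illustration borrows another outcome's scale.** The 7.4 and 13.1 belong to fNIRS, which already has a mixed model, and the correlation and dropout odds are assumed. A reader might infer a marked loss of power. With +7.4 and no ETV data, simulated power does fall from about 78–79% to about 68–69% (odds ratio 2) or 64% (odds ratio 3). Section D, however, powers for a decrease. With −7.4 and the same dropout rule, power rises to about 86–87% or 90%, because the effect is exaggerated. Neither result transfers to the affected outcomes.

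**Conclusion.** The concern holds in a limited form. For DVA, laser speckle and FMD, and cognition, the named GLM fitted on complete pairs cannot include participants who have neither Visit 2 nor ETV data. That fits poorly with the intent-to-treat statement and the planned 20% dropout.

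The number affected lies between 0 and 6–7 of 32, depending on ETV attendance and on whether ETV values are used. If dropout is unrelated to baseline, the cost is a 2 to 3% larger standard error and no bias, given an assumed correlation of 0.5. If dropout depends on baseline, the estimate is biased, with a direction set by the sign of the effect and the dropout mechanism.

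The protocol gives no effect size, SD or power for these outcomes, so no power loss can be claimed for them. The change is still worth making: it is nearly free, it concerns part of the primary hypothesis, and it replaces a stated method with one that better serves the plan's own aim.

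**What to change.** In the DVA, endothelial function and cognition paragraphs of Section M:

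1. Replace the repeated-measures GLM with a linear mixed model fitted by REML, with Visit as a fixed effect and a random subject intercept, including every participant with at least one measurement.
2. State that ETV measurements enter as the post-baseline value, and acknowledge that they may be taken before month 6.
3. Report the Visit 2 minus Visit 1 contrast with a 95% confidence interval.

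Write the model out in full rather than referring to the fNIRS model: the fNIRS formula has a Group term and a random subject term but no Visit term, so copying it would not yield this contrast. Section D instructs all participants to follow TRE, so the between-group factor in these paragraphs has to be reconciled with the design in the same edit.

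The cost is wording in three paragraphs, with no new data and no additional participants. The analysis then relies on a missing-at-random assumption, which should be stated.
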